### Biological sampling

A 15-ml blood sample will be collected from each participant at the screening visit and approximately 40 ml will be collected during test visits 1 and 2. Table 3 outlines the blood parameters that are analysed in each study visit.

Participants collect-24 hour urine samples, which will be used to investigate the bioavailability of key polyphenol compounds present in the capsules. In addition, hydration status is measured using urine osmolality and urine dip stick from both the urine collected over 24 hours and from the single urine sample collected during test visits 1 and 2.

### Data analysis

A consort flowchart of enrolled participants will be provided, and the demographic characteristics recorded at the time of randomisation will also be described. Descriptive analysis will be conducted for all baseline variables to compare participants in both study groups. Results will be reported as means and standard deviations for continuous variables and frequencies with percentages for categorical variables. Two group comparisons for changes in primary and secondary outcome measures following 12 weeks of intervention will be made, assuming similar levels of variance between the two treatment groups and using two-tailed t-tests for normally distributed data. Paired t-tests will be used to assess within-group changes in study outcomes. Multiple linear regression models will be used to assess whether changes from baseline to 12 weeks were significant between the study groups. Regression analysis will be conducted, with adjustment for potential baseline confounding variables. Additionally, a sensitivity analysis will be performed, exploring variation in the standard deviation between the differences of the mean change in cIMT measurements. Exploratory within-group changes will also be assessed for each outcome measure.

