**Methods/Design:**

This is a double-blind, randomised controlled trial that includes overweight and obese but otherwise healthy participants. Participants are randomly allocated to one of two groups: active supplementation (encapsulated fruit and vegetable powder) or placebo taken twice daily for 12 weeks, whereas both groups will be given the ‘5-A-Day’ dietary advice. The primary outcome is to measure changes to the carotid intima media thickness (cIMT) between the two groups from baseline (test visit 1) to 12 weeks later (test visit 2). The secondary outcomes include macro- and microvascular changes and changes to blood markers.

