### Sample size

The sample size calculation was performed according to cIMT changes over 12 weeks of supplementation. cIMT normal values in the general adult population (including overweight individuals) less than 65 years of age, range from 0.60 to 0.80 mm with a SD of 0.10 mm. [7]. Assuming a two-tailed t-test using a 5 % significance level (two-sided), a sample size of 37 in each group (74 participants in total) was determined to have 85 % power to detect a mean cIMT difference of 0.07 mm after 12 weeks of supplementation between the intervention and control groups, assuming a common SD of 0.10 mm. Allowing for a dropout rate of approximately 15 %, we aim to recruit 80 participants in total; *n* = 40 in the placebo and *n* = 40 in the intervention group.

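### Two between-group analyses are planned for the primary cIMT question, neither is named as decisive, and baseline cIMT is not stated as a covariate

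*Protocol article*

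**What the plan says.** The abstract of the protocol article (Methods/Design) defines the primary outcome as the between-group comparison of change in cIMT from test visit 1 to week 12.

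For that question the Data analysis section gives two routes:

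- **Unadjusted comparison of change.** "Two group comparisons for changes in primary and secondary outcome measures following 12 weeks of intervention will be made". The test is an equal-variance, two-tailed t-test, for normally distributed data.
- **Regression on change.** "Multiple linear regression models will be used to assess whether changes from baseline to 12 weeks were significant between the study groups". The next sentence adds: "Regression analysis will be conducted, with adjustment for potential baseline confounding variables". These two sentences read most naturally as one adjusted model.

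The section does not rank the two routes and names no covariate. The Sample size section plans on a two-sided t-test at 5 % with 37 per group, for "85 % power to detect a mean cIMT difference of 0.07 mm after 12 weeks of supplementation between the intervention and control groups". Table 2 schedules cIMT at both test visits, so the baseline value is due to be measured in every participant.

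**The concern.** An unadjusted and an adjusted p-value for the same primary comparison can fall on opposite sides of 5 %, and the article does not say which would then count. If the more favourable one were reported, the error rate of the primary claim would exceed its stated level.

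The second issue is efficiency. A raw change score subtracts the whole baseline value, whereas only a fraction r of it predicts the follow-up value (with equal SDs at both visits). A chance difference between the groups at baseline therefore carries into the estimate through regression to the mean. Adjusting for baseline cIMT removes this and uses a measurement that the trial takes anyway.

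The word used for the covariates also points the wrong way. In a randomised trial, baseline differences arise by chance, so covariates should be named in advance for their prognostic value and not as confounders.

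**Working it through.** **Inputs from the Sample size section.** Difference 0.07 mm; SD 0.10 mm, taken from population cIMT values ("range from 0.60 to 0.80 mm with a SD of 0.10 mm"); two-sided alpha 5 %; power 85 %; 37 per group. Recruitment: "Allowing for a dropout rate of approximately 15 %, we aim to recruit 80 participants in total". If that loss occurs, 80 × 0.85 = 68 remain, or 34 per group.

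**Assumption.** The correlation r between baseline and week-12 cIMT is not in the document. A range is shown, with SD 0.10 mm at both visits.

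**1. The plan's own figure.** n per group = 2 × (1.960 + 1.036)² × 0.10² / 0.07² = 36.6, so 37. Power at 37 per group is 85.3 % by normal approximation and 84.4 % by the exact t distribution. The stated sample size reproduces.

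**2. SD under each analysis.**

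- t-test on change: 0.10 × √(2(1 − r))
- regression with baseline cIMT (ANCOVA): 0.10 × √(1 − r²)
- variance ratio, ANCOVA to change: (1 − r²) / (2(1 − r)) = (1 + r)/2

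The ratio cannot exceed 1. The SD of change equals the planning SD of 0.10 mm only at r = 0.5.

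**3. Power for 0.07 mm at 34 per group (exact t).**

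| r (assumed) | SD change | SD ANCOVA | Variance saved | Power, change | Power, ANCOVA |
|---|---|---|---|---|---|
| 0.3 | 0.118 | 0.095 | 35 % | 67 % | 85 % |
| 0.5 | 0.100 | 0.087 | 25 % | 81 % | 91 % |
| 0.7 | 0.077 | 0.071 | 15 % | 96 % | 98 % |
| 0.9 | 0.045 | 0.044 | 5 % | about 100 % | about 100 % |

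At the full 37 per group the pattern is the same: 84 % against 93 % at r = 0.5, and 97 % against 99 % at r = 0.7.

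**4. Effect of a chance baseline imbalance.** The standard error of the baseline difference at 34 per group is 0.10 × √(2/34) = 0.024 mm. An imbalance of one standard error shifts the change-score estimate by (1 − r) × 0.024 mm:

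- r = 0.5: 0.012 mm, 17 % of the 0.07 mm target
- r = 0.7: 0.007 mm, 10 %
- r = 0.9: 0.002 mm, 3 %

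**5. Type I error if the smaller p-value is reported.** In 20,000 simulated null trials per setting, at 37 per group, each test alone rejected in about 5 % (4.8–5.1 %). Taking the smaller p-value of the t-test on change and the baseline-adjusted model rejected in 7.3 % (r = 0.5), 6.7 % (r = 0.7) and 6.0 % (r = 0.9).

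**The case against.** The strongest reply is that nothing here is an error. The t-test on change matches the outcome as defined, is unbiased under randomisation and holds its 5 % level. A covariate list, and even the ranking of models, may sit in a statistical analysis plan that is not shown. The regression may already be the recommended model: baseline cIMT could be among the unnamed covariates, and regressing change on group and baseline gives the same treatment coefficient as regressing week-12 cIMT on them. If r is high, the gain is trivial. All of this stands, and it limits the size of the point.

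It also rules out some stronger readings that a reader might infer:

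- *That the unadjusted t-test is the primary analysis.* It is listed first and matches the sample size calculation, but the article never labels it so.
- *That three analyses compete.* The two regression sentences read as one model, which leaves two between-group analyses.
- *That covariates will be picked by observed baseline differences.* The section describes baseline variables by group and later mentions adjustment, but states no rule that links the two.
- *That baseline cIMT is left out.* It is unnamed, not excluded.
- *That the error rate will be inflated.* The 6–7 % applies only if the smaller p-value is chosen, which the article does not propose.

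Blinding helps only in part. The Randomisation and blinding section keeps allocation concealed until analysis is complete, which hinders choosing by direction of effect. It does not prevent choosing by p-value, because two-sided p-values need only coded groups.

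What remains does not depend on an absent list. The article itself sets out two tests of one primary question without an order between them, and one of the two forgoes a baseline value that is already scheduled.

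**Conclusion.** The point holds at moderate severity. The primary cIMT question has two stated between-group analyses and no rule for which decides. That ambiguity exists at any value of r, and its cost if exploited is a type I error of about 6–7 %.

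The precision argument is conditional. It rests on an assumed r, on equal SDs of 0.10 mm at both visits and, for the 34 per group, on the 15 % dropout that the article allows for. Adjustment is worth about ten percentage points of power at r = 0.5, about two at r = 0.7 and nothing visible at r = 0.9. If r is below 0.5, the t-test on change falls short of the planned 85 % power even at 37 per group (71 % at r = 0.3), whereas the adjusted model does not (88 %).

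This is a better method available at no cost. It does not show that the t-test on change is invalid.

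**What to change.** In the Data analysis section:

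1. Name one primary analysis: linear regression of week-12 cIMT (or change in cIMT) on treatment group and baseline cIMT, reporting the group coefficient with its 95 % confidence interval.
2. List any further covariates, chosen for prognostic value, and fix them before any outcome data are analysed. Fixing them before unblinding is not enough here, because allocation stays concealed until the analysis is finished.
3. Use the same form for each continuous secondary outcome, with that outcome's own baseline value.
4. Label the unadjusted t-test on change and any other adjusted model as supportive.

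The cost is analysis wording only. cIMT is already scheduled at both test visits, so no new measurement is needed. Enrolment was still ongoing when the article was submitted, so as of that date the change could be made before results were known.

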#### Screening visit

Following completion of the pre-screening questionnaire and provided that the participant is eligible to take part in the study, he/she is asked to attend the screening visit, which takes place at HNR and lasts approximately 2 hours.

Informed consent is obtained from all participants during the screening visit, and any questions relating to the study are answered, ensuring that the participant has fully understood all the study procedures before continuing. Consent is obtained before any measurements are taken. Height is measured to the nearest 0.1 cm using a stadiometer, and weight to the nearest 0.1 kg using calibrated mass scales. BMI is calculated using these measurements. Two blood pressure readings are recorded while the patient is in a seated position. A third BP measurement is performed if the first two readings have a discrepancy of more than 10 mmHg.

A full eligibility assessment is carried out using the HNR volunteer health screening and demographics questionnaire. Medical history and any recent changes in medication since the pre-screening questionnaire are also assessed and evaluated at this stage. In addition, female participants are also asked about the timing of their menstrual cycle as this can affect the vascular measurements in the study. Fasting blood samples are collected by venepuncture to measure blood lipids, glucose, and liver function as a routine safety measure and as an indicator of normal metabolism. Table 3 summarises all the blood markers that are examined during the study. At the end of the visit, the volunteers are asked to complete two short questionnaires: the International Physical Activity Questionnaire (IPAQ) and the Five-a-day Community Evaluation Tool (FACET) and are provided with ‘5-A-Day’ dietary advice. If successfully screened, the participant is invited back to complete test visits 1 and 2. Ineligible participants are thanked for their time and are offered to join the HNR volunteer database. Breakfast is provided to all potential volunteers before the end of the visit.

**Table 3 Tab3:** Blood parameters analysed in the National Safety Associates nutritional supplementation trial of fruit and vegetable extracts and vascular function (NNTV) study

	Biological parameter	Screening visit	Test visit 1 (week 0)	Intermediate visit (week 6)	Test visit 2 (week 12)
Screening/Safety and Research	FBC	X	X	-	X
	HbA1c	X	X	-	X
	HDL	X	X	-	X
	LDL	X	X	-	X
	Total cholesterol	X	X	-	X

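### For the blood markers and FACET measured twice before the first capsule, modelling the week-12 value on both earlier values would be more precise than the planned t-test on changes (optional, secondary outcomes only)

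*Protocol article*

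**What the plan says.** The Data analysis section plans two-group comparisons of changes in primary and secondary outcomes after 12 weeks, using two-tailed t-tests for normally distributed data. It adds multiple linear regression to "assess whether changes from baseline to 12 weeks were significant between the study groups", adjusted for baseline confounders that it does not name.

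Baseline is defined only in the abstract, for cIMT: "from baseline (test visit 1) to 12 weeks later (test visit 2".

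Table 3 has a block headed "Screening/Safety and Research" that marks FBC, HbA1c, HDL, LDL, total cholesterol, ALT, creatinine, fasting glucose and potassium at screening, test visit 1 and test visit 2. For questionnaires, the Screening visit section says that "the volunteers are asked to complete two short questionnaires: the International Physical Activity Questionnaire (IPAQ) and the Five-a-day Community Evaluation Tool (FACET"). Table 2 repeats both at test visit 1. Capsules are handed out only at the end of test visit 1.

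The Aim/Objectives section lists laboratory blood markers, FACET, and safety indicators (liver function, routine bloods including full blood count) as secondary objectives. IPAQ is not listed there.

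**The concern.** A change from a single baseline visit uses one earlier value per person. These outcomes have two, both taken before treatment and both likely to predict the week-12 value. A simple change also fixes the slope on baseline at 1, so it passes on more within-person noise than a model that estimates the slope. The sample size was set for cIMT alone, so the secondary comparisons have whatever precision about 74 completers give. At stake are wider confidence intervals than necessary on the metabolic, routine-blood and FACET comparisons. Bias is not at stake.

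**Working it through.** **The plan's own figure.** "Assuming a two-tailed t-test using a 5 % significance level (two-sided), a sample size of 37 in each group" is stated to give "85 % power to detect a mean cIMT difference of 0.07 mm after 12 weeks of supplementation", "assuming a common SD of 0.10 mm". Check: 2 × (1.960 + 1.036)² × (0.10/0.07)² = 2 × 8.978 × 2.041 = 36.6, so 37 per group. Power at 37 is 85.3 % by the normal approximation and 84.4 % by the noncentral t. The figure reproduces. It concerns cIMT, which is not measured at screening, so nothing below changes it.

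**Inputs for this point.** The visits come from Tables 2 and 3. The between-visit correlation r is not given anywhere; 0.5 to 0.9 is assumed.

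**Case 1: equal correlation r between all three visits.** The variance of the group difference, in units of 2σ²/n, is:
- change from one baseline: 2(1 − r)
- ANCOVA on one baseline: 1 − r²
- ANCOVA on both pre-capsule values: 1 − 2r²/(1 + r)

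| r | Change score | ANCOVA, one value | ANCOVA, two values | Cut, change to two values | Cut, one to two values |
|---|---|---|---|---|---|
| 0.5 | 1.000 | 0.750 | 0.667 | 33 % | 11 % |
| 0.6 | 0.800 | 0.640 | 0.550 | 31 % | 14 % |
| 0.7 | 0.600 | 0.510 | 0.424 | 29 % | 17 % |
| 0.8 | 0.400 | 0.360 | 0.289 | 28 % | 20 % |
| 0.9 | 0.200 | 0.190 | 0.147 | 26 % | 22 % |

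Moving from the change score to single-baseline ANCOVA multiplies the variance by (1 + r)/2, a cut of 25 % at r = 0.5 and 5 % at r = 0.9. ANCOVA itself therefore supplies most of the gain at low r, and the second value most of it at high r. In interval width, √0.667 = 0.816 and √0.737 = 0.858, so confidence intervals are 18 % to 14 % narrower than with the change score.

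**Case 2: screening correlates 0.1 less with week 12.** This is plausible because screening is further away in time and 5-A-Day advice is given at the end of that visit. The correlations of test visit 1 with screening and with week 12 stay at r; write s = r − 0.1. The two-covariate variance is 1 − (s² + r² − 2r·s·r)/(1 − r²). At r = 0.5, s = 0.4: 1 − (0.16 + 0.25 − 0.20)/0.75 = 0.72. A change from the mean of both values has variance 1 + (1 + r)/2 − (r + s).

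| r | s | Change score | ANCOVA, one value | ANCOVA, two values | Change from mean of both | Cut, change to two values | Cut, one to two values |
|---|---|---|---|---|---|---|---|
| 0.5 | 0.4 | 1.000 | 0.750 | 0.720 | 0.850 | 28 % | 4 % |
| 0.7 | 0.6 | 0.600 | 0.510 | 0.486 | 0.550 | 19 % | 5 % |
| 0.8 | 0.7 | 0.400 | 0.360 | 0.350 | 0.400 | 12.5 % | 3 % |
| 0.9 | 0.8 | 0.200 | 0.190 | 0.1895 | 0.250 | 5 % | 0.3 % |

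Averaging the two values gains nothing at r = 0.8 and raises the variance by 25 % at r = 0.9. Two separate slopes avoid this.

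**Selection at screening.** Deranged screening bloods can exclude a participant. In a simulation with r = 0.7 and the top 10 % of screening values removed, the two-value to one-value ANCOVA ratio is 0.86, against 0.83 without exclusion. The gain is largely kept.

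**Cost.** With 74 completers the t-test has 72 residual degrees of freedom and the two-covariate model 70. One degree of freedom in about 70 is roughly 1.4 %, so at the weakest setting (r = 0.9, s = 0.8) the second value pays nothing net, while the model still does no worse than the change score.

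**The case against.** The strongest reply is that the article contains no error here. It plans regression with adjustment for unnamed baseline variables, and these could include the test visit 1 value or the screening value. A regression of change on group that includes the outcome's own baseline gives the same treatment effect as ANCOVA. The choice may also sit in an analysis plan that is not shown. This stands in part: the article does not rule the screening value out. It does, however, name the t-test on changes for secondary outcomes, and that stated method can be improved.

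A reader might infer more than the document supports:
- **That the screening values are wasted.** They serve eligibility and safety, as the Screening visit section says, and the planned adjustment leaves room for them.
- **That a change score can use only one earlier value.** A change from the mean of two baselines is an ordinary change score. Its variance is 1.5(1 − r) under equal correlation, a 25 % cut.
- **That the planned analysis is the least efficient unbiased one.** Comparing week-12 values alone is also unbiased, with variance 1 in these units. The change score ties with it at r = 0.5 and beats it at every higher r.
- **That the whole 26 % to 33 % comes from the second measurement.** Part of it comes from ANCOVA on one baseline.
- **That IPAQ is affected.** It is taken at both visits but is not a listed outcome.

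Equal correlation is also the favourable assumption, which is why Case 2 is shown.

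**Conclusion.** The point holds as an optional, nearly free improvement for the nine blood rows and FACET. Against the t-test on changes, the two-covariate model cuts the variance by 33 % to 26 % under equal correlation of 0.5 to 0.9, and by about 28 % to 5 % if screening correlates 0.1 less with week 12. The second pre-capsule value itself adds 11 % to 22 % in the first case and 0 to 5 % in the second, relative to single-baseline ANCOVA. All these figures rest on assumed correlations and on a roughly linear relation between visits; the article does not describe how FACET is scored. The planned randomised comparison is valid, and the primary outcome, its sample size and its power are untouched.

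**What to change.** For FBC, HbA1c, HDL, LDL, total cholesterol, ALT, creatinine, glucose, potassium and FACET, replace the t-test on changes with a linear model of the week-12 value on randomised group, with the test visit 1 value and the screening value as two separate covariates. Do not average them: 5-A-Day advice falls between the two, and averaging can lose precision. Outcomes without a screening value can take the test visit 1 value as a single covariate in the same form. IPAQ and the week-6 FACET score need no place in this change.

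The cost is one sentence of analysis wording, fixed before unblinding, and one or two degrees of freedom. It needs no new data or participants and adds no bias, since both covariates precede the first capsule.

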## Discussion

This study was designed to test the hypothesis that supplementation with capsules containing a combination of fruit and vegetables, in addition to dietary advice to consume five portions of fruit and vegetables daily, will significantly modulate biomarkers of vascular and metabolic function in overweight and obese adults, compared with a control group receiving identical dietary advice to consume ‘5-A-Day’ and placebo capsules. The particular population was chosen for this study as overweight and obese individuals have increased cytokines free fatty acids and inflammation markers. These increases can lead to early endothelial dysfunction due to increased inflammation and other mechanisms associated with overweight and obesity.

This study was powered with cIMT as a primary outcome. However, as cIMT is a dynamic but structural measurement, a number of functional measurements, including those assessing vascular endothelium and smooth muscle tone, as well as both factors together, form part of the panel of outcome measures used in this mechanistic trial. These measures were designed to provide novel insights into vascular function pathways and the prediction of cardiovascular risk. In addition to vascular measurements, waist circumference, blood pressure and hydration status are expected to provide complementary information.

In particular, this explanatory trial also incorporates potential novel biomarkers such as trimethylamine-N-oxide (TMAO) and lipopolysaccharide (LPS). Polyphenolic compounds have recently been found to modulate TMAO [11, 12]. Evaluating the ability of the NNTV study interventions on TMAO concentrations might be useful to understand if the polyphenolic fraction of this extract acts as a gut microbial modulator, reducing cardiovascular disease risk through the control of trimethylamine production.

Lipopolysaccharide (LPS), also known as endotoxin, is a component of the cell wall of gram-negative bacteria that may normally reside in the colon of humans. Additionally, polyphenolic compounds have been attributed to modulation of the gut microbiome, through mechanisms involving their bacteriostatic activity and the inhibition of microbial fermentation [11, 12]. Assessing the ability of the fruit and vegetable extract to change levels of LPS can help explain if the polyphenolic fraction of this extract acts as a gut microbial modulator, reducing future disease risk through the control of endotoxaemia.

